## Abstract

**Background:**

In 1999, type 2 diabetes mellitus (T2DM) was identified as an emerging epidemic in youth, and racial and ethnic minority youth were identified with high risk. Two decades later, no gold standard T2DM prevention intervention has been established for this population.

**Objective:**

This study tests the efficacy of a telehealth diabetes prevention intervention for African American (AA) families with children with risk for T2DM. Concurrently, investigators aim to evaluate an implementation strategy for the uptake of the intervention by the University of Mississippi Medical Center’s (UMMC) pediatric weight management clinic.

**Methods:**

This single-arm trial will enroll 20 parents with overweight or obesity of children (8-11 years) with overweight or obesity, both of whom are at risk for T2DM. Parents will meet in small groups (5 parents per group) weekly for 11 weeks and then monthly for 4 monthly maintenance sessions via videoconference using Wi-Fi–enabled iPads with cellular connectivity. The intervention will be adapted from the National Diabetes Prevention Program and *Power to Prevent*, a diabetes prevention program tailored for AA families. The same lifestyle intervention facilitated by a racially concordant lifestyle coach trained in the Diabetes Prevention Program will be delivered to all groups (n=4). Participants will be recruited in-person during patient encounters at the UMMC’s pediatric weight management clinic. Sessions will consist of dietary and physical activity behavior change strategies facilitated using problem-solving and goal-setting skills. The implementation strategy has 2 targets: the pediatric weight management clinic site and clinical team and parents of children at risk for T2DM engaged in intensive obesity treatment to prevent T2DM. The multifaceted implementation protocol includes 4 discrete strategies: creating a new clinical team, changing the service site, intervening with families, and promoting organizational readiness for change.

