The power calculation, across 5 scenarios, shows detectable effect sizes, ≥−2.5 (SD 0.05) BMI in parents [58] and in children, where a modest reduction in BMI z score (≥0 to <−0.1, SD 0.05) has been associated with improved cardiometabolic risk [59]. In the first 3 scenarios, assuming 10% attrition [37], a minimum of 18 dyads are needed. In scenarios 4 and 5, detectable effect sizes are reported in the case of 0% (n=20 dyads) and 20% (n=16 dyads) attrition. We anticipate 20% attrition, which is consistent with the group- and family-based telehealth lifestyle intervention literature [60-62]. Analyses are based on α=.05 and a conservative two-sided test. An effect size of 1.0 is considered substantial and 0.5 is considered medium. We will obtain reliable effect size estimates to design a pilot randomized controlled trial.

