#### Intervention Sessions

Group sessions will consist of identifying behavior change strategies leading to achieving the intervention targets (20 minutes), problem solving and decision making to circumvent barriers (20 minutes), and family goal setting and action planning (20 minutes). Parents will be coached to self-select behavior change strategies and practice skills that will enable them to do things such as making healthy foods available in the home, modifying recipes to be healthier, reading food labels, increasing family physical activity, and creating boundaries for the use of technology to reduce out-of-school sedentary time. Parents will be encouraged to use behavioral reinforcement strategies with their children, such as giving immediate praise, creating realistic expectations, and rewarding effort [77]. The practice of brainstorming will be used to encourage parents as a collective group to self-discover solutions to behavior change barriers and support participants in achieving their goals. Brainstorming has proven to be an effective component of problem solving and mitigating barriers to sustainable behavior change [78-82]. Action planning will be used to facilitate parents in setting realistic, attainable, and short-term (weekly) goals for making dietary and physical activity changes. Goal setting positively correlates with weight loss [83], and action planning is an effective self-monitoring strategy that will allow participants to personalize their goals and gradually achieve intervention targets [84,85].

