#### Intervention Participant Retention

Telehealth is an effective retention strategy used in the DPP [86] and mitigates transportation barriers [87]. The lifestyle coach will dedicate time outside of intervention sessions to build rapport with parents and will function as a personal contact for participants to establish meaningful relationships, send meeting reminders, and schedule and conduct make-up sessions (consistent with DPP [63]) [86]. Participants will be incentivized using attendance raffles for cooking (eg, measuring cups), physical activity equipment (eg, jump rope), and incremental monetary compensation at each assessment point (baseline, US $50; postintervention, US $75; follow-up, US $150) [86]. Study assessments will be conducted in-person at the time of the child’s routine appointment with the pediatric weight management clinic and monetary resources will be allocated to families experiencing transportation barriers.

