### Data Analysis

Participant sociodemographic characteristics at baseline will be described using means and SDs, medians and ranges, or frequencies with percentages where applicable. The primary outcome evaluation will assess the change in child BMI *z* score (index participant) and parent BMI (coparticipant) from baseline to 12 and 30 weeks using repeated measures analysis of covariance with child Tanner stage as the covariate. Secondary analyses will include the comparison of anthropometric, biomarker, behavioral, psychosocial, and environmental measures adjusted for other factors. Generalized linear modeling will be used to assess the effect of the intervention, both unadjusted and adjusted (controlling for demographics, baseline BMI *z* score, and BMI). Data will be analyzed according to intention-to-treat principles [106-108].

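### Parents are treated in four interacting video groups, but neither the power paragraph nor the named models allow for correlation within a group, so the implied standard errors and detectable effects are too favourable

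*Protocol article*

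**What the plan says.** The abstract (Methods) fixes the delivery: "Parents will meet in small groups (5 parents per group) weekly for 11 weeks", followed by monthly maintenance sessions. The same programme is "facilitated by a racially concordant lifestyle coach trained in the Diabetes Prevention Program will be delivered to all groups (n=4"), so 20 parents form 4 groups of 5. Interaction among group members is part of the treatment. Under Intervention Sessions: "The practice of brainstorming will be used to encourage parents as a collective group to self-discover solutions to behavior change barriers".

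Participant Recruitment and Sample Size counts dyads only: 20 with no attrition, 18 with 10% and 16 with 20%, the last being the rate the investigators anticipate. It sets alpha at .05, two-sided. It states no power level, ICC or design effect. The same paragraph says that the trial should yield reliable effect size estimates for designing a randomised pilot.

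The Data Analysis section on efficacy outcomes assesses change in both primary outcomes "using repeated measures analysis of covariance with child Tanner stage as the covariate". Generalized linear models follow, unadjusted and adjusted for demographics, baseline BMI z score and BMI. Video group appears in none of these, and no random effect or cluster-robust variance is named.

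**The concern.** Parents in one group share sessions, peers and the solutions that the group arrives at, so their changes may resemble each other more than those of parents in different groups. A positive correlation of this kind makes the variance of the mean change larger than the variance for the same number of independent dyads. A model without a group term does not see the extra variance. Its intervals come out too narrow, and its tests reject more often than the stated 5%.

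In a single-arm pilot the p-value matters less than the interval around the change, because that interval tells the next trial's designers how much to trust the estimate. An interval computed as if the groups did not exist overstates what four groups can show.

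**Working it through.** **Inputs from the protocol article.** Four groups of 5; 20, 18 or 16 dyads analysed; two-sided alpha .05.

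**Assumed inputs, not in the article.** ICC of the change within a video group: 0.05 and 0.10, with 0.02 and 0.20 as outer values. Power: 80%. Equal group sizes, m = n/4.

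**1. The article's own figures.** 20 × 0.90 = 18 and 20 × 0.80 = 16, so the dyad counts follow from attrition. The statement that 18 dyads are needed cannot be reproduced, because neither the target power nor the scenarios' effect sizes in SD units are given. As a reference, a one-sample t test of change on independent dyads, by the noncentral t at 80% power, detects 0.66 SD (n=20), 0.70 SD (n=18) and 0.75 SD (n=16).

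**2. Design effect and effective sample size.** Design effect = 1 + (m − 1) × ICC; effective n = n / design effect.

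- n=20, m=5: ICC 0.05 gives 1 + 4 × 0.05 = 1.20 and 20/1.20 = 16.7. ICC 0.10 gives 1.40 and 14.3.
- n=18, m=4.5: 1.175 and 15.3; 1.35 and 13.3.
- n=16, m=4: 1.15 and 13.9; 1.30 and 12.3.

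The standard error grows by the square root of the design effect. At n=20 that is a factor of 1.095 (ICC 0.05) or 1.183 (ICC 0.10).

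**3. Detectable effect at 80% power, in SD of change.** The lower figure of each pair keeps n − 1 degrees of freedom; the higher uses effective n − 1.

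| Dyads | ICC 0 | ICC 0.05 | ICC 0.10 |
|---|---|---|---|
| 20 | 0.66 | 0.72–0.73 | 0.78–0.80 |
| 18 | 0.70 | 0.76–0.77 | 0.81–0.83 |
| 16 | 0.75 | 0.80–0.81 | 0.86–0.88 |

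If inference rests on the four groups with 3 df, the figures at n=20 are 1.04 (ICC 0.05) and 1.13 (ICC 0.10), above the effect of 1.0 that the article calls substantial.

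**4. Type I error when the groups are ignored.** Simulation with 200,000 replicates, no true change, and an ordinary one-sample t test:

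| Layout | ICC 0.02 | ICC 0.05 | ICC 0.10 | ICC 0.20 |
|---|---|---|---|---|
| 4 groups of 5 | 5.9% | 7.1% | 9.6% | 14.5% |
| 4 groups of 4 | 5.7% | 6.7% | 8.4% | 12.0% |

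A t test on the four group means stays at about 5% throughout.

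**5. Interval width at n=18.** The 95% half-width is 0.50 SD if dyads are independent. With n − 1 df it is 0.54 SD at ICC 0.05 and 0.58 SD at ICC 0.10. With 3 df it is 0.81 and 0.87 SD.

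**6. What clustering leaves alone.** The mean change is not biased. With 4 groups of 5, the expected sample variance is the true variance × [1 − ICC × 4/19]. At ICC 0.10 the bracket is 0.979, so the SD is about 1% low; at ICC 0.20 it is 0.958, about 2% low.

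**The case against.** **A fuller plan may contain the group term.** Only a journal article is at hand, and it never asserts independence. That is fair, and a random effect or a small-sample correction could well sit in an analysis plan. But the article does name a primary model, list the adjustment variables and give a basis for its sample size, and all three omit a feature of its own design.

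**No printed figure is shown to be wrong.** This stands. No power level or interval width is stated, and both the 80% and the ICC are assumptions. The criticism concerns the precision that the dyad counts imply.

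**On the printed inputs clustering hardly matters.** Also true. The child figures (0.1 with SD 0.05) make an effect of 2 SD, for which power stays at or above 97.8% even with ICC 0.20 and 3 df. The parent figures, where the paragraph "shows detectable effect sizes, ≥−2.5 (SD 0.05) BMI in parents", make 2.5/0.05 = 50 SD. These SDs are a separate and larger problem in that paragraph, and they give no assurance about power for realistic effects.

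**Children do not attend.** Sessions are held with parents, so any group effect reaches the child's BMI z score only through the parent. The ICC for that outcome may be smaller.

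**Four groups estimate an ICC poorly.** Correct. This is why the group-level analysis is best kept as a sensitivity analysis, but it does not justify working as if the ICC were zero.

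A reader might also infer more than the article supports:

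- That the groups are closed. The article does not say so, and its make-up sessions and individual outreach may dilute the correlation.
- That the single coach worsens precision. A coach common to all groups adds no between-coach variance within this trial.
- That the phrase "Analyses are based on α=.05 and a conservative two-sided test" is a false claim about clustering. It most naturally contrasts two-sided with one-sided testing.
- That the effect size handed to the next trial would be too optimistic. Step 6 of the working shows that the mean and SD are barely touched.

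**Conclusion.** The point holds in a limited form. The design creates four interacting groups, and the stated sample size basis and the named models make no allowance for them. With any positive within-group correlation, the standard errors are too small and the detectable effects implied by 20, 18 or 16 dyads are too favourable.

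With an assumed ICC of 0.05 to 0.10, the true type I error of a nominal 5% test is about 7% to 10% with 20 dyads, and the detectable effect at 80% power grows by roughly 10% to 20% in relative terms (from 0.66 to 0.72–0.80 SD). With an ICC of 0.02 the error rate is only about 5.9%. The size of the problem therefore rests on a correlation that the article does not give and that may be lower for the child outcome. The point should be addressed because the remedy is cheap and the estimates are meant to inform a later trial. It does not undermine the pilot.

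**What to change.** In Participant Recruitment and Sample Size, show the detectable effects in SD units for ICC 0, 0.05 and 0.10 at 20, 18 and 16 dyads, with the ICC values labelled as assumed and the power level stated.

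In the efficacy Data Analysis section, keep the planned model and prespecify one sensitivity analysis for both primary outcomes. Either of two will do: video group as a random effect with small-sample degrees of freedom, or the four group mean changes analysed on 3 df. Report the estimated ICC with its interval, described as a rough input to later planning only.

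The cost is a few lines of text and one extra model for each primary outcome. The downside is that the detectable effects look less favourable and that the group-level interval will be wide with four groups.

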**Results:**

Recruitment and enrollment began in December 2020, and the intervention is scheduled to be delivered to the first cohort of parents in March 2021. The results are expected to be submitted for publication beginning in November 2021 through 2022. The primary outcome measure for the pilot trial will include changes from baseline to 12 and 30 weeks in the child BMI *z* score and parent BMI. The implementation evaluation will include multiple measures of feasibility, acceptability, appropriateness, fidelity, and efficacy. This protocol was approved by the UMMC’s Institutional Review Board (#2020V0249).

**Conclusions:**

The proposed intervention approach is supported by the scientific literature and is scalable given the current and future health care subsidies for telehealth. Findings from this pilot trial will begin to address critical barriers to defining a gold standard lifestyle intervention for AA families with children at risk for T2DM. If effective, the intervention could be feasibly disseminated to treat obesity and prevent T2DM in high-risk AA pediatric populations.

**International Registered Report Identifier (IRRID):**

PRR1-10.2196/25699

## Introduction

### Background

In 1999, Rosenbloom and Winter [1] labeled type 2 diabetes mellitus (T2DM) in youth as an emerging epidemic, identifying racial and ethnic minority groups, whose proportion in the US population continues to increase [2], at highest risk. T2DM is a chronic state of hyperglycemia that clusters in families because of genetic, cultural, behavioral, and environmental risk factors [3,4]. In 2018, an estimated 32.4 million (10.5%) people of all ages in the United States had T2DM, and an additional 88 million adults (34.5%; ≥18 years) and 1 in 5 youths (12-18 years) were estimated to have had prediabetes [5,6]. Predictions indicate that with rising incidence rates, the proportion of US youth (<20 years) with T2DM may quadruple between 2010 (22,820 youths) and 2050 (84,131 youths [7]), and African American (AA) youth represent a vulnerable pediatric population with high risk [7,8].

Alarmingly, T2DM presents a more severe and aggressive disease course in youth than in adults [9], and there is no optimal treatment for T2DM in youth [10]. In a retrospective analysis of youth and adults with obesity and impaired glucose tolerance, adolescents experienced more severe insulin resistance than adults with similar adiposity and glycemic status [9]. Of particular concern are the results from the recent RISE (Restoring Insulin Secretion) Pediatric Medication Study that evaluated whether β-cell function and metabolic control could be effectively altered by a pharmacological intervention [11]. Results from this randomized controlled trial with 91 pubertal youths (10-19 years) with obesity and existing impaired glucose tolerance randomized to 12 months of metformin showed that the early pharmacologic intervention was ineffective in slowing disease progression [11]. These findings underscore the need for strategies to prevent or delay the onset of T2DM in youth at high risk [12].

Prediabetes is a precursor to T2DM, characterized by hyperglycemic parameters below the diabetes threshold [13,14]. An estimated 5% to 10% of prediabetes cases advance to T2DM per annum [15], and according to the American Diabetes Association (ADA), up to 70% of people with prediabetes will progress to T2DM at some point in their lifetime [16]. Although prediabetes may never progress to T2DM, unfavorable cardiometabolic profiles remain among people with prediabetes, putting them at increased risk for cardiovascular-related morbidities and premature mortality [17]. Consequently, youth with prediabetes are faced with earlier and prolonged exposure to myriad cardiometabolic abnormalities, accentuating the critical need for obesity treatment in the primary prevention of T2DM in youth [7,10].

### Diabetes Prevention

Studies have indicated that adults with prediabetes can mitigate T2DM prognosis by taking preventive action, such as participation in the National Diabetes Prevention Program (DPP) [18]. The DPP began as a multisite randomized controlled trial, which demonstrated the effectiveness of a 12-month intensive lifestyle intervention over pharmaceutical treatment for preventing or delaying T2DM among adult participants with prediabetes across all racial and ethnic groups [19]. At 2.8- and 10-year follow-up, participants randomized to the lifestyle intervention group reduced their risk of developing T2DM by 58% and 34% compared with 31% and 18% in the metformin group, respectively [20,21]. In 2010, US Congress authorized the Centers for Disease Control and Prevention to lead the dissemination of the DPP [18] as a targeted strategy and population approach to reduce the incidence of T2DM among adults with prediabetes [22].

Intensive lifestyle modification is the recommended treatment for pediatric patients with prediabetes [23]; however, there is no gold standard lifestyle intervention to prevent T2DM in youth. Previous studies have demonstrated the feasibility of lifestyle interventions for youth with overweight or obesity and those at risk for T2DM and the importance of tailored interventions for racial and ethnic minority groups; however, limited efficacy has been shown in reducing T2DM risk and improving obesity outcomes [24-26]. Intervention studies with youth have also been hindered by the insufficient representation of racial and ethnic minority youth at high risk for T2DM in obesity treatment trials [27]. *Power to Prevent* is a diabetes prevention intervention from the Centers for Disease Control and Prevention based on the DPP and tailored for AA families [28]. To our knowledge, this intervention has not yet been evaluated among AA families with children at risk for T2DM or disseminated through health care institutions. Given the restrictions on in-person gatherings because of the COVID-19 pandemic and the consistent literature reporting high attrition rates among in-person interventions, there is a need for novel and sustainable implementation modalities for delivering lifestyle interventions to racial and ethnic minority families at high risk for T2DM [24].

Telehealth has demonstrated effectiveness in delivering obesity and prediabetes treatment [29-33] and has mitigated barriers to accessing care for millions of Americans [31]. In particular, videoconferencing has been widely used to deliver effective T2DM care for adult and young patients [33-36] and has recently established efficacy for group-based interventions [37-39]. In a review of 17 lifestyle intervention studies, the authors found that tablet-based group videoconferencing was feasible, accessible, and acceptable, regardless of participants’ digital literacy (technology skills) [37]. Across studies, videoconferencing groups cultivated cohesiveness and bonding similar to in-person settings, and participants developed behavioral skills including lifestyle behaviors to treat obesity and demonstrated improved health outcomes along with high attendance rates (66%-93.8%) and few dropouts [37]. Intervention group sizes averaged from 5 to 7 participants and met weekly for 1 hour over 12 to 26 sessions in total [37]. The use of telehealth technology to deliver a family-based lifestyle diabetes prevention intervention tailored for AA families is likely to offer a scalable approach to reduce T2DM among high-risk youth [40-42].

### Objectives

The Telehealth Diabetes Prevention Intervention for the Next Generation of African American Youth (TELE-GEN) pilot trial proposes implementing and evaluating a diabetes prevention intervention based on the *Power to Prevent* program for AA parents of children (8-11 years) who are both overweight or obese and at risk for T2DM. Historically, a lengthy effectiveness study conducted under *ideal circumstances* would be the next step in identifying a gold standard lifestyle intervention to prevent T2DM in AA youth; however, standard effectiveness studies are limited by their inability for rapid translation and the need for subsequent implementation studies to validate utility in real-world settings [43]. Hybrid research designs leverage the rigor of clinical trials and implementation science to foster rapid translation and effective implementation [33,43]. Thus, in partnership with the Center for Telehealth at the University of Mississippi Medical Center (UMMC) and pediatric weight management clinic, we propose a novel effectiveness-implementation hybrid type II research design [43] with the coprimary aim to (1) conduct a 30-week, single-arm pilot trial with at-risk parents of at-risk children to assess the early efficacy of Power to Prevent delivered using small group-based videoconferencing to reduce BMI in parents (n=20) and stabilize or reduce BMI z scores in children (n=20), while (2) conducting a comprehensive evaluation of a multifaceted implementation strategy for the uptake of the intervention by the pediatric weight management clinic at the UMMC in Jackson, Mississippi. The protocol described below was approved by the UMMC’s Institutional Review Board (#2020V0249).

